|  |  | Adjusted odds ratio (95% confidence interval) | | p-value |
| IY vs. PInC | | x.xx (x.xx, x.xx) | | x.xxxx |

Table 4.1.2 Secondary outcome – ECBI problem score. ITT population with 12-month follow-up.

Table 4.2.1 Secondary outcome – ECBI intensity score. ITT population.

Table 4.2.2 Secondary outcome – ECBI intensity score. ITT population with 12-month follow-up.

Table 4.3.1 Secondary outcome - SDQ. ITT population.

Table 4.3.2 Secondary outcome - SDQ. ITT population with 12-month follow-up.

Table 4.3.3 Secondary outcome – SDQ using repeat baseline values where available. ITT population.

Table 4.4.1 Secondary outcome - GHQ. ITT population.

Table 4.4.2 Secondary outcome - GHQ. ITT population with 12-month follow-up.

Table 4.5.1 Secondary outcome – Parental ASRS Part A. ITT population.

Table 4.5.2 Secondary outcome – Parental ASRS Part A. ITT population with 12-month follow-up.

Table 4.6.1 Secondary outcome – Parental ASRS Part B. ITT population.

Table 4.6.2 Secondary outcome – Parental ASRS Part B. ITT population with 12-month follow-up.

Table 4.7.1 Secondary outcome – PDHS challenging behaviour intensity. ITT population.

Table 4.7.2 Secondary outcome - PDHS challenging behaviour intensity. ITT population with 12-month follow-up.

Table 4.7.3 Secondary outcome – PDHS challenging behaviour intensity using repeat baseline values where available. ITT population.

Table 4.8.1 Secondary outcome – PDHS challenging behaviour frequency. ITT population.

Table 4.8.2 Secondary outcome - PDHS challenging behaviour frequency. ITT population with 12-month follow-up.

Table 4.8.3 Secondary outcome – PDHS challenging behaviour frequency using repeat baseline values where available. ITT population.

Table 4.9.1 Secondary outcome – PDHS parenting tasks intensity. ITT population.

Table 4.9.2 Secondary outcome - PDHS parenting tasks intensity. ITT population with 12-month follow-up.

Table 4.9.3 Secondary outcome – PDHS parenting tasks intensity using repeat baseline values where available. ITT population.

Table 4.10.1 Secondary outcome – PDHS parenting tasks intensity. ITT population.

Table 4.10.2 Secondary outcome - PDHS parenting tasks intensity. ITT population with 12-month follow-up.

Table 4.10.3 Secondary outcome – PDHS parenting tasks intensity using repeat baseline values where available. ITT population.

Table 4.11.1 Secondary outcome – CORC-GBO. ITT population.

|  |  |  | Randomised intervention | |
| --- | --- | --- | --- | --- |
|  |  | All | PInC | IY |
| Baseline in goal which improved most | N_OBS_ (N_MISS_)  Mean (SD)  Median (IQR)  [Range] | nn (nn)  xx.x (xx.x)  xx.x (xx.x, xx.x)  [xx.x, xx.x] | nn (nn)  xx.x (xx.x)  xx.x (xx.x, xx.x)  [xx.x, xx.x] | nn (nn)  xx.x (xx.x)  xx.x (xx.x, xx.x)  [xx.x, xx.x] |
| Baseline in goal which improved least | N_OBS_ (N_MISS_)  Mean (SD)  Median (IQR)  [Range] | nn (nn)  xx.x (xx.x)  xx.x (xx.x, xx.x)  [xx.x, xx.x] | nn (nn)  xx.x (xx.x)  xx.x (xx.x, xx.x)  [xx.x, xx.x] | nn (nn)  xx.x (xx.x)  xx.x (xx.x, xx.x)  [xx.x, xx.x] |
| Average baseline across all goals | N_OBS_ (N_MISS_)  Mean (SD)  Median (IQR)  [Range] | nn (nn)  xx.x (xx.x)  xx.x (xx.x, xx.x)  [xx.x, xx.x] | nn (nn)  xx.x (xx.x)  xx.x (xx.x, xx.x)  [xx.x, xx.x] | nn (nn)  xx.x (xx.x)  xx.x (xx.x, xx.x)  [xx.x, xx.x] |
| Follow-up in goal which improved most | N_OBS_ (N_MISS_)  Mean (SD)  Median (IQR)  [Range] | nn (nn)  xx.x (xx.x)  xx.x (xx.x, xx.x)  [xx.x, xx.x] | nn (nn)  xx.x (xx.x)  xx.x (xx.x, xx.x)  [xx.x, xx.x] | nn (nn)  xx.x (xx.x)  xx.x (xx.x, xx.x)  [xx.x, xx.x] |
| Follow-up in goal which improved least | N_OBS_ (N_MISS_)  Mean (SD)  Median (IQR)  [Range] | nn (nn)  xx.x (xx.x)  xx.x (xx.x, xx.x)  [xx.x, xx.x] | nn (nn)  xx.x (xx.x)  xx.x (xx.x, xx.x)  [xx.x, xx.x] | nn (nn)  xx.x (xx.x)  xx.x (xx.x, xx.x)  [xx.x, xx.x] |
| Average follow-up across all goals | N_OBS_ (N_MISS_)  Mean (SD)  Median (IQR)  [Range] | nn (nn)  xx.x (xx.x)  xx.x (xx.x, xx.x)  [xx.x, xx.x] | nn (nn)  xx.x (xx.x)  xx.x (xx.x, xx.x)  [xx.x, xx.x] | nn (nn)  xx.x (xx.x)  xx.x (xx.x, xx.x)  [xx.x, xx.x] |
| Participants with baseline and follow-up data only | | | | |
| N |  | nn | nn | Nn |
| Baseline in goal which improved most | N_OBS_ (N_MISS_)  Mean (SD)  Median (IQR)  [Range] | nn (nn)  xx.x (xx.x)  xx.x (xx.x, xx.x)  [xx.x, xx.x] | nn (nn)  xx.x (xx.x)  xx.x (xx.x, xx.x)  [xx.x, xx.x] | nn (nn)  xx.x (xx.x)  xx.x (xx.x, xx.x)  [xx.x, xx.x] |
| Baseline in goal which improved least | N_OBS_ (N_MISS_)  Mean (SD)  Median (IQR)  [Range] | nn (nn)  xx.x (xx.x)  xx.x (xx.x, xx.x)  [xx.x, xx.x] | nn (nn)  xx.x (xx.x)  xx.x (xx.x, xx.x)  [xx.x, xx.x] | nn (nn)  xx.x (xx.x)  xx.x (xx.x, xx.x)  [xx.x, xx.x] |
| Average baseline across all goals | N_OBS_ (N_MISS_)  Mean (SD)  Median (IQR)  [Range] | nn (nn)  xx.x (xx.x)  xx.x (xx.x, xx.x)  [xx.x, xx.x] | nn (nn)  xx.x (xx.x)  xx.x (xx.x, xx.x)  [xx.x, xx.x] | nn (nn)  xx.x (xx.x)  xx.x (xx.x, xx.x)  [xx.x, xx.x] |
| Follow-up in goal which improved most | N_OBS_ (N_MISS_)  Mean (SD)  Median (IQR)  [Range] | nn (nn)  xx.x (xx.x)  xx.x (xx.x, xx.x)  [xx.x, xx.x] | nn (nn)  xx.x (xx.x)  xx.x (xx.x, xx.x)  [xx.x, xx.x] | nn (nn)  xx.x (xx.x)  xx.x (xx.x, xx.x)  [xx.x, xx.x] |
| Follow-up in goal which improved least | N_OBS_ (N_MISS_)  Mean (SD)  Median (IQR)  [Range] | nn (nn)  xx.x (xx.x)  xx.x (xx.x, xx.x)  [xx.x, xx.x] | nn (nn)  xx.x (xx.x)  xx.x (xx.x, xx.x)  [xx.x, xx.x] | nn (nn)  xx.x (xx.x)  xx.x (xx.x, xx.x)  [xx.x, xx.x] |
| Average follow-up across all goals | N_OBS_ (N_MISS_)  Mean (SD)  Median (IQR)  [Range] | nn (nn)  xx.x (xx.x)  xx.x (xx.x, xx.x)  [xx.x, xx.x] | nn (nn)  xx.x (xx.x)  xx.x (xx.x, xx.x)  [xx.x, xx.x] | nn (nn)  xx.x (xx.x)  xx.x (xx.x, xx.x)  [xx.x, xx.x] |
| Change from baseline in goal which improved most | Mean (SD)  Median (IQR)  [Range] | xx.x (xx.x)  xx.x (xx.x, xx.x)  [xx.x, xx.x] | xx.x (xx.x)  xx.x (xx.x, xx.x)  [xx.x, xx.x] | xx.x (xx.x)  xx.x (xx.x, xx.x)  [xx.x, xx.x] |
| Change from baseline in goal which improved least | Mean (SD)  Median (IQR)  [Range] | xx.x (xx.x)  xx.x (xx.x, xx.x)  [xx.x, xx.x] | xx.x (xx.x)  xx.x (xx.x, xx.x)  [xx.x, xx.x] | xx.x (xx.x)  xx.x (xx.x, xx.x)  [xx.x, xx.x] |
| Average change from baseline across all goals | Mean (SD)  Median (IQR)  [Range] | xx.x (xx.x)  xx.x (xx.x, xx.x)  [xx.x, xx.x] | xx.x (xx.x)  xx.x (xx.x, xx.x)  [xx.x, xx.x] | xx.x (xx.x)  xx.x (xx.x, xx.x)  [xx.x, xx.x] |

Table 4.11.2 Secondary outcome – CORC-GBO. ITT population with 12-month follow-up.

Table 4.12.1 Secondary outcome – EQ-5D. ITT population.

Table 4.12.2 Secondary outcome – EQ-5D. ITT population with 12-month follow-up.

Table 4.13.1 Secondary outcome - PedsQL psychosocial health summary score. ITT population.

Table 4.13.2 Secondary outcome - PedsQL psychosocial health summary score. ITT population with 12-month follow-up.

Table 4.14.1 Secondary outcome - PedsQL physical health summary score. ITT population.

Table 4.14.2 Secondary outcome - PedsQL physical health summary score. ITT population with 12-month follow-up.

Table 4.15.1 Secondary outcome - PedsQL total score. ITT population.

Table 4.15.2 Secondary outcome - PedsQL total score. ITT population with 12-month follow-up.

Table 5.1 Attendance at group sessions

|  |  |  | Randomised intervention | |
| --- | --- | --- | --- | --- |
|  |  | All | PInC | IY |
| Proportion of sessions attended (%) | N_OBS_ (N_MISS_)  Mean (SD)  Median (IQR)  [Range] | nn (nn)  xx.x (xx.x)  xx.x (xx.x, xx.x)  [xx.x, xx.x] | nn (nn)  xx.x (xx.x)  xx.x (xx.x, xx.x)  [xx.x, xx.x] | nn (nn)  xx.x (xx.x)  xx.x (xx.x, xx.x)  [xx.x, xx.x] |

Table 5.2 Attendance at group sessions by sessions – PinC

| Session | Number not withdrawn | Number attended | Percentage attended |
| --- | --- | --- | --- |
| Week 1 | nn | nn | xx.x |
| Week 2 | nn | nn | xx.x |
| Week 3 | nn | nn | xx.x |
| Week 4 | nn | nn | xx.x |
| Week 5 | nn | nn | xx.x |
| Follow-up | nn | nn | xx.x |
| Attended at least 2 sessions | nn | nn | xx.x |

Table 5.3 Attendance at group sessions by sessions – IY

| Session | Number not withdrawn | Number attended | Percentage attended |
| --- | --- | --- | --- |
| Week 1 | nn | nn | xx.x |
| Week 2 | nn | nn | xx.x |
| Week 3 | nn | Nn | xx.x |
| Week 4 | nn | Nn | xx.x |
| Week 5 | nn | Nn | xx.x |
| … | … | … | … |
| Week 14 | nn | Nn | xx.x |
| Attended at least 7 sessions | nn | Nn | xx.x |

Table 6.1 Withdrawals from the intervention

|  |  |  | Randomised intervention | |
| --- | --- | --- | --- | --- |
|  |  | All | PInC | IY |
| Withdrawals | N_OBS_ (N_MISS_)  N(%) No  N(%) Yes | nn (nn)  nn (xx.x)  nn (xx.x) | nn (nn)  nn (xx.x)  nn (xx.x) | nn (nn)  nn (xx.x)  nn (xx.x) |
| Withdrawal reasons | N_OBS_ (N_MISS_)  N(%) Wished to attend another intervention  N(%) Didn’t want to continue  N(%) Couldn’t attend due to ill health  N(%) time commitment  N(%) No reason given | nn (nn)  nn (xx.x)  nn (xx.x) | nn (nn)  nn (xx.x)  nn (xx.x) | nn (nn)  nn (xx.x)  nn (xx.x) |

Table 6.2 Withdrawals from the study

|  |  |  | Randomised intervention | |
| --- | --- | --- | --- | --- |
|  |  | All | PInC | IY |
| Withdrawals | N_OBS_ (N_MISS_)  N(%) No  N(%) Yes | nn (nn)  nn (xx.x)  nn (xx.x) | nn (nn)  nn (xx.x)  nn (xx.x) | nn (nn)  nn (xx.x)  nn (xx.x) |
| Withdrawal reasons | N_OBS_ (N_MISS_)  N(%) Unhappy with baseline questionnaire  N(%) Too busy  N(%) Did not attend baseline assessment… | nn (nn)  nn (xx.x)  nn (xx.x)  nn (xx.x) | nn (nn)  nn (xx.x)  nn (xx.x)  nn (xx.x) | nn (nn)  nn (xx.x)  nn (xx.x)  nn (xx.x) |

Table 7 Summary of adverse events

|  |  |  | Randomised intervention | |
| --- | --- | --- | --- | --- |
|  |  | All | PInC | IY |
| Participants experiencing at least one SAE | N(%) | nn (xx.x) | nn (xx.x) | nn (xx.x) |
| Number of events | N | nn | nn | nn |
| Required hospitalisation | N(%) | nn (xx.x) | nn (xx.x) | nn (xx.x) |
| … | … | … | … | … |
| Severity | N_OBS_ (N_MISS_)  N(%) Mild  N(%) Moderate  N(%) Severe | nn (nn)  nn (xx.x)  nn (xx.x)  nn (xx.x) | nn (nn)  nn (xx.x)  nn (xx.x)  nn (xx.x) | nn (nn)  nn (xx.x)  nn (xx.x)  nn (xx.x) |
| Expectedness | N_OBS_ (N_MISS_)  N(%) Expected  N(%) Unexpected | nn (nn)  nn (xx.x)  nn (xx.x) | nn (nn)  nn (xx.x)  nn (xx.x) | nn (nn)  nn (xx.x)  nn (xx.x) |
| Relation to intervention | N_OBS_ (N_MISS_)  N(%) Related  N(%) Unrelated | nn (nn)  nn (xx.x)  nn (xx.x) | nn (nn)  nn (xx.x)  nn (xx.x) | nn (nn)  nn (xx.x)  nn (xx.x) |
| Outcome | N_OBS_ (N_MISS_)  N(%) Recovered  N(%) Recovered with sequelae  N(%) Recovering  N(%) Not recovered  N(%) Fatal | nn (nn)  nn (xx.x)  nn (xx.x)  nn (xx.x)  nn (xx.x)  nn (xx.x) | nn (nn)  nn (xx.x)  nn (xx.x)  nn (xx.x)  nn (xx.x)  nn (xx.x) | nn (nn)  nn (xx.x)  nn (xx.x)  nn (xx.x)  nn (xx.x)  nn (xx.x) |
| Duration (days) | N_OBS_ (N_MISS_)  Mean (SD)  Median (IQR)  [Range] | nn (nn)  xx.x (xx.x)  xx.x (xx.x, xx.x)  [xx.x, xx.x] | nn (nn)  xx.x (xx.x)  xx.x (xx.x, xx.x)  [xx.x, xx.x] | nn (nn)  xx.x (xx.x)  xx.x (xx.x, xx.x)  [xx.x, xx.x] |

Table 8 Medications

|  |  |  | Randomised intervention | |
| --- | --- | --- | --- | --- |
|  |  | All | PInC | IY |
| Medication 1 | N(%) | nn (xx.x) | nn (xx.x) | nn (xx.x) |
| … |  |  |  |  |

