## Study Objectives

This study is a feasibility trial aiming to address the following research questions:

1. Are parents of children recently diagnosed with ADHD willing to be randomised to PInC or IY?
2. Can sufficient numbers of families be (a) recruited and (b) retained such that a full‐scale RCT is likely to be feasible?
3. Are research procedures and measures feasible and acceptable to participating families?

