## Feasibility Outcomes

The outcomes related to feasibility are

- Consent rate among all families that were approached;
- Retention rate among all consenting families;
- Completeness of the putative outcome measures for a full trial.

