# Analysis populations

## Efficacy

The intention-to-treat (ITT) population will consist of all participants who consented and provided any baseline data.

The per-protocol (PP) population will consist of all participants who consented and provided any baseline data and attended at least seven out of 14 sessions for IY or two out of six sessions for PInC.

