## Feasibility outcomes

The following proportions will be calculated:

- the proportion of eligible subjects that was approached;
- the proportion of approached subjects who consented to take part in the trial;
- the proportion of approached subjects who consented to take part in the trial and provide any baseline data;
- the proportion of consented participants who provide any follow-up data;
- the proportion of consented participants in wave 1, 2 and 3 who provide any follow-up data at 12 months;
- the proportion of consented participants in wave 4 who provide any follow-up data at 6 months;
- the proportion of consented participants who provide outcome data for each of the efficacy outcomes separately, overall and by waves 1-3 vs. wave 4.

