# Table Templates

Table 1.1 Recruitment. Proportions reported in % with 95% confidence interval.

|  | N | Proportion |
| --- | --- | --- |
| Eligible subjects in research period | nn |  |
| Approached subjects (out of all eligible subjects) | nn | xx.x (xx.x – xx.x) |
| Subjects consented (out of all subjects approached) | nn | xx.x (xx.x – xx.x) |
| Subjects consented with baseline data (out of all subjects approached) | nn | xx.x (xx.x – xx.x) |

Table 1.2 Retention. Proportions are out of all who consented and have any baseline data (ITT population), reported in % with 95% confidence interval.

|  |  | | Randomised intervention | | | |
| --- | --- | --- | --- | --- | --- | --- |
|  | All | | PInC | | IY | |
|  | N | Proportion | N | Proportion | N | Proportion |
| Randomised | nn |  | nn |  | Nn |  |
| Provide any follow-up data | nn | xx.x (xx.x – xx.x) | nn | xx.x (xx.x – xx.x) | nn | xx.x (xx.x – xx.x) |
| Provide follow-up data for |  |  |  |  |  |  |
| PSOC | nn | xx.x (xx.x – xx.x) | nn | xx.x (xx.x – xx.x) | nn | xx.x (xx.x – xx.x) |
| ECBI problem score | nn | xx.x (xx.x – xx.x) | nn | xx.x (xx.x – xx.x) | nn | xx.x (xx.x – xx.x) |
| ECBI intensity score | nn | xx.x (xx.x – xx.x) | nn | xx.x (xx.x – xx.x) | nn | xx.x (xx.x – xx.x) |
| SDQ | nn | xx.x (xx.x – xx.x) | nn | xx.x (xx.x – xx.x) | nn | xx.x (xx.x – xx.x) |
| GHQ | nn | xx.x (xx.x – xx.x) | nn | xx.x (xx.x – xx.x) | nn | xx.x (xx.x – xx.x) |
| ASRS (parent) Part A | nn | xx.x (xx.x – xx.x) | nn | xx.x (xx.x – xx.x) | nn | xx.x (xx.x – xx.x) |
| ASRS (parent) Part B | nn | xx.x (xx.x – xx.x) | nn | xx.x (xx.x – xx.x) | nn | xx.x (xx.x – xx.x) |
| PDHS challenging behaviour intensity | nn | xx.x (xx.x – xx.x) | nn | xx.x (xx.x – xx.x) | nn | xx.x (xx.x – xx.x) |
| PDHS challenging behaviour frequency | nn | xx.x (xx.x – xx.x) | nn | xx.x (xx.x – xx.x) | nn | xx.x (xx.x – xx.x) |
| PDHS parenting tasks intensity | nn | xx.x (xx.x – xx.x) | nn | xx.x (xx.x – xx.x) | nn | xx.x (xx.x – xx.x) |
| PDHS parenting tasks frequency | nn | xx.x (xx.x – xx.x) | nn | xx.x (xx.x – xx.x) | nn | xx.x (xx.x – xx.x) |
| CORC-GBO | nn | xx.x (xx.x – xx.x) | nn | xx.x (xx.x – xx.x) | nn | xx.x (xx.x – xx.x) |
| EQ-5D-5L | nn | xx.x (xx.x – xx.x) | nn | xx.x (xx.x – xx.x) | nn | xx.x (xx.x – xx.x) |
| PedsQL psychosocial health summary score | nn | xx.x (xx.x – xx.x) | nn | xx.x (xx.x – xx.x) | nn | xx.x (xx.x – xx.x) |

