| PedsQL physical health summary score | nn | xx.x (xx.x – xx.x) | nn | xx.x (xx.x – xx.x) | nn | xx.x (xx.x – xx.x) |
| PedsQL total score | nn | xx.x (xx.x – xx.x) | nn | xx.x (xx.x – xx.x) | nn | xx.x (xx.x – xx.x) |

Table 1.3 Retention – waves 1-3. Proportions are out of all who consented and have any baseline data (ITT population), reported in % with 95% confidence interval.

|  |  | | Randomised intervention | | | |
| --- | --- | --- | --- | --- | --- | --- |
|  | All | | PInC | | IY | |
|  | N | Proportion | N | Proportion | N | Proportion |
| Randomised | nn |  | nn |  | Nn |  |
| Provide any follow-up data | nn | xx.x (xx.x – xx.x) | nn | xx.x (xx.x – xx.x) | nn | xx.x (xx.x – xx.x) |
| Provide follow-up data for |  |  |  |  |  |  |
| PSOC | nn | xx.x (xx.x – xx.x) | nn | xx.x (xx.x – xx.x) | nn | xx.x (xx.x – xx.x) |
| ECBI problem score | nn | xx.x (xx.x – xx.x) | nn | xx.x (xx.x – xx.x) | nn | xx.x (xx.x – xx.x) |
| ECBI intensity score | nn | xx.x (xx.x – xx.x) | nn | xx.x (xx.x – xx.x) | nn | xx.x (xx.x – xx.x) |
| SDQ | nn | xx.x (xx.x – xx.x) | nn | xx.x (xx.x – xx.x) | nn | xx.x (xx.x – xx.x) |
| GHQ | nn | xx.x (xx.x – xx.x) | nn | xx.x (xx.x – xx.x) | nn | xx.x (xx.x – xx.x) |
| ASRS (parent) Part A | nn | xx.x (xx.x – xx.x) | nn | xx.x (xx.x – xx.x) | nn | xx.x (xx.x – xx.x) |
| ASRS (parent) Part B | nn | xx.x (xx.x – xx.x) | nn | xx.x (xx.x – xx.x) | nn | xx.x (xx.x – xx.x) |
| PDHS challenging behaviour intensity | nn | xx.x (xx.x – xx.x) | nn | xx.x (xx.x – xx.x) | nn | xx.x (xx.x – xx.x) |
| PDHS challenging behaviour frequency | nn | xx.x (xx.x – xx.x) | nn | xx.x (xx.x – xx.x) | nn | xx.x (xx.x – xx.x) |
| PDHS parenting tasks intensity | nn | xx.x (xx.x – xx.x) | nn | xx.x (xx.x – xx.x) | nn | xx.x (xx.x – xx.x) |
| PDHS parenting tasks frequency | nn | xx.x (xx.x – xx.x) | nn | xx.x (xx.x – xx.x) | nn | xx.x (xx.x – xx.x) |
| CORC-GBO | nn | xx.x (xx.x – xx.x) | nn | xx.x (xx.x – xx.x) | nn | xx.x (xx.x – xx.x) |
| EQ-5D-5L | nn | xx.x (xx.x – xx.x) | nn | xx.x (xx.x – xx.x) | nn | xx.x (xx.x – xx.x) |
| PedsQL psychosocial health summary score | nn | xx.x (xx.x – xx.x) | nn | xx.x (xx.x – xx.x) | nn | xx.x (xx.x – xx.x) |
| PedsQL physical health summary score | nn | xx.x (xx.x – xx.x) | nn | xx.x (xx.x – xx.x) | nn | xx.x (xx.x – xx.x) |
| PedsQL total score | nn | xx.x (xx.x – xx.x) | nn | xx.x (xx.x – xx.x) | nn | xx.x (xx.x – xx.x) |

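### Tables 1.2 to 1.4 compute retention and completeness out of families with baseline data, whereas the SAP defines both out of all consenting families

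*Supplement*

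**What the plan says.** The Feasibility Outcomes list in the SAP introduction gives the "Retention rate among all consenting families". Section 3.3 turns this into proportions to be calculated. One is "the proportion of consented participants who provide any follow-up data", with separate versions for waves 1 to 3 at 12 months and wave 4 at 6 months. Another is "the proportion of consented participants who provide outcome data for each of the efficacy outcomes separately, overall and by waves 1-3 vs. wave 4". All of these take consented participants as the base.

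The shells in section 7 take a different base. The caption of the main retention table reads "Table 1.2 Retention. Proportions are out of all who consented and have any baseline data (ITT population"), and that of the next reads "Table 1.3 Retention – waves 1-3. Proportions are out of all who consented and have any baseline data (ITT population"). Table 1.4, for wave 4, has the same wording. Section 2.1 defines that set: "The intention-to-treat (ITT) population will consist of all participants who consented and provided any baseline data".

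The SAP treats the two groups as distinct. Table 1.1 has one row for those who consented and another for those who consented and have baseline data. Section 2.2 makes the safety population all who consented. Table 6.2 lists "Did not attend baseline assessment" among the reasons for withdrawing from the study.

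**The concern.** Retention answers part (b) of research question 2, whether enough families can be kept for a full-scale trial to be feasible. A family that consents and then drops out before baseline is a retention failure under the SAP's own definition. Under the captions of Tables 1.2 to 1.4 that family leaves the denominator and no longer counts as a loss. The same applies to every completeness row in those tables.

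The planning assumption in Sample Size and Power applies two-thirds retention to everyone who responds. A rate that starts only at baseline is a different quantity and should not be set against it. The programmer will fill in the shells, so unless the captions change, the outcome will not be reported as defined. Settling the denominator after the data are seen would also invite criticism.

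**Working it through.** **Inputs.** From Sample Size and Power: 100 families approached, 60% response, two-thirds retention, 20 families per arm. From Randomisation: 1:1 allocation. From General Principles: Clopper-Pearson 95% intervals. The number of consenting families with neither baseline nor follow-up data, *m*, is not in the SAP. It is an assumption here, varied from 0 to 12 of 60.

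**Step 1: reproduce the plan's figure.** 100 × 0.60 = 60 consenting; 60 × 2/3 = 40 retained; 40 / 2 = 20 per arm. This matches the SAP. The two-thirds therefore has all 60 responders as its base, the same base as the outcome definition.

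**Step 2: compare the two rates.** The defined rate is 40/60. The rate in the shell is 40/(60 − *m*).

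| *m* (assumed) | Shell rate | 95% CI | Excess over 66.7%, points |
| --- | --- | --- | --- |
| 0 | 40/60 = 66.7% | 53.3 to 78.3 | 0.0 |
| 3 | 40/57 = 70.2% | 56.6 to 81.6 | 3.5 |
| 5 | 40/55 = 72.7% | 59.0 to 83.9 | 6.1 |
| 6 | 40/54 = 74.1% | 60.3 to 85.0 | 7.4 |
| 10 | 40/50 = 80.0% | 66.3 to 90.0 | 13.3 |
| 12 | 40/48 = 83.3% | 69.8 to 92.5 | 16.7 |

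**Step 3: read it the other way.** With *m* = 6, a tabulated 36/54 = 66.7% would appear to meet the planning assumption. Out of all consenting families it is 36/60 = 60.0%, or 18 per arm instead of 20.

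**Step 4: by arm.** Suppose all 60 are randomised before baseline, 30 per arm, and 20 per arm are followed up. Each arm then retains 20/30 = 66.7% (47.2 to 82.7). If 1 family in one arm and 5 in the other lack baseline data, the shell shows 20/29 = 69.0% and 20/25 = 80.0%. That is an apparent difference of 11.0 points where none exists. If randomisation follows baseline, families lost before baseline have no arm and this illustration does not apply.

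**Step 5: can the direction reverse?** Let *k* of the *m* families without baseline data still give follow-up data, with 40 followed up in all and the shell counting only ITT members. With *m* = 6 the shell rate is (40 − *k*)/54. It is 74.1% at *k* = 0, 66.7% at *k* = 4 and 64.8% at *k* = 5. The shell rate falls below the defined rate only if at least 5 of the 6 who missed baseline return for follow-up, which is implausible.

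**The case against.** The best defence is that the governing text is already right. Section 3.3 states the consented denominator, the captions state theirs openly, and the early losses are not hidden. Table 1.1 shows the gap between consenting and giving baseline data, section 3.1 tabulates the ITT and safety populations, and Table 6.2 reports withdrawals before baseline. A reader could divide the follow-up count in Table 1.2 by the consented count in Table 1.1, provided that follow-up count is not itself limited to ITT members. This stands, and it makes the point an inconsistency in the shells and not a flawed analysis. It does not dispose of the point: Table 1.1 has no split by arm or wave group, so those rates cannot be rebuilt, and no shell shows retention as defined.

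Some stronger readings are tempting but unsupported:

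- A reader might infer that reported retention is inflated, or inflated by a known amount. The SAP does not say how many consenting families lack baseline data, and the number may be zero.
- Table 6.2 also lists dissatisfaction with the baseline questionnaire. This does not show that a family gave no baseline data, because any baseline data keep it in the ITT set.
- A reader might infer that research question 1, "Are parents of children recently diagnosed with ADHD willing to be randomised to PInC or IY", goes unanswered because the row for randomised families has no proportion. Consent to a 1:1 randomised trial is already estimated among those approached, with an interval, in Table 1.1.
- A reader might conclude that the ITT population must be redefined by randomisation. The SAP does not give the timing of randomisation relative to baseline, and the protocol is not among the documents. That is a separate question which these passages cannot settle.

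**Conclusion.** The contradiction is certain: the definition and section 3.3 use one denominator, and the captions of three tables use another. Its numerical effect is conditional. It is zero if every consenting family gives baseline data. Otherwise, at the planned 60 consenting and 40 followed up, it is 3.5 points for 3 missing families, 6.1 for 5 and 13.3 for 10, assuming those families also give no follow-up data. The effect is upward in any plausible case. No numerical progression threshold appears in the SAP, so a change of denominator would not flip a stated rule. The harm is a feasibility outcome tabulated off its definition and not comparable with the planning figure.

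**What to change.** Change the captions and denominators of Tables 1.2, 1.3 and 1.4 to all consented participants, as section 3.3 states. Keep the ITT-based proportion, if wanted, only as a clearly labelled secondary row. If some consenting families are not randomised, they belong to no arm. In that case label the arm-column denominator explicitly as all randomised and show the number consented but not randomised, so that the arm columns can be reconciled with the overall column. The text of section 3.3 needs no change.

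The cost is table-shell wording, with no extra data collection, and possibly a less favourable retention figure. The change should be made before the data are analysed.
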